Community-based EDs in two regions will develop, implement, and prospectively evaluate a web-based CDS tool (Appy-CDS) for children with acute abdominal pain. Appy-CDS will identify pediatric patients with acute abdominal pain at increased risk for appendicitis, notify providers of a patient's estimated risk for appendicitis, and provide specific evidence-based recommendations. To measure the impact of Appy-CDS, we will conduct a cluster- randomized trial across 17 participating EDs in two large health systems with a combined total of more than 90,000 pediatric visits per year.

Specific Aim 1: To design and implement a triage-based trigger, as part of Appy-CDS, to identify pediatric patients with acute abdominal pain at increased risk for appendicitis.

- Hypothesis 1: Among pediatric patients with abdominal pain, a triage-based trigger will identify those at risk for appendicitis with a negative predictive value  $\geq 99\%$  and positive predictive value  $\geq 20\%$ .

Specific Aim 2: To evaluate the impact of the full Appy-CDS intervention on appropriate use of diagnostic imaging (CT and ultrasound) for pediatric patients with acute abdominal pain at risk for appendicitis.

- Hypothesis 2. Among eligible pediatric patients at risk for appendicitis, those treated at intervention EDs compared to those treated at control EDs will be less likely to undergo a CT examination.

- Hypothesis 3. Among eligible pediatric patients at risk for appendicitis, those treated at intervention EDs compared to those treated at control EDs will be less likely to undergo diagnostic imaging with CT or ultrasound.

**Specific Aim 3:** To evaluate the impact of the full Appy-CDS intervention on health care costs.

- Hypothesis 4. Among pediatric patients at risk for appendicitis, those treated at intervention EDs compared to those treated at control EDs will have significantly lower resource use in a defined 7-day period after an index ED visit.

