**Reduction in CT use** (Hypothesis 2): Among pediatric patients identified through the Appy-CDS as at risk for appendicitis, receipt of an abdominal and/or pelvic CT during the index ED visit will be determined through completed orders in Epic. We will identify CTs obtained using the following CPT codes: 74150, 74160, 74170, 74174, 74176, 74177, 72192, 72193, and 72194. Only CTs ordered in the ED will be included.

**Total Imaging Utilization** (Hypothesis 3): Among pediatric patients identified through the Appy-CDS as at risk for appendicitis, receipt of an abdominal and/or pelvic CT or abdominal and/or pelvic ultrasound during the index ED visit will be determined through completed orders in Epic. We will identify CTs as described above and ultrasounds using the following CPT codes: 76705, 76700, 76770, 76775, 76857, 76830, and 76856. Only ultrasounds ordered in the ED will be included.

**Direct medical expenditures** (Hypothesis 4): For HP and KPNC members, utilization of all medical services within 7 days of the index ED visit will be captured from insurance claims data. Hospital-based costs at the study sites for nonmembers will be assessed using Total Care Relative Resource Value units (TCRRVs), described in detail below. While the goals of the CDS are to reduce CT use, the CDS may inadvertently lead to overuse of other diagnostic tests. In addition, by discouraging CT, the CDS may result in prolonged ED or inpatient observation. To capture all potential costs related to the treatment episode, we will include all utilization of health care services occurring at the ED visit and during the subsequent 7 days. This time window is adequate to include the most common complications associated with an appendiceal perforation. Across both participating health systems, coding guidelines and incentives ensure that all services provided should be accurate in the claims data. Although we do not anticipate differences in appendectomy or adverse event rates related to initiation of the Appy-CDS, if this does occur, we will assess the potential long- term impact of these differences by modeling long-term impact over a 12- and 24-month timeframe.

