#### d) Recommendations by Risk Group

The table below outlines the recommendations used in the HP full CDS by risk threshold.

| Risk   | Category      | Proportion | Clinical recommendations                                                                              |
|--------|---------------|------------|-------------------------------------------------------------------------------------------------------|
| <5%    | Ultra Low     | 37%        | Outpatient, no diagnostic imaging                                                                     |
| 6-15%  | Low           | 16%        | ED observation for 4-6 hours; no imaging; outpatient follow-up                                        |
| 16-25% | Low moderate  | 10%        | Pain <24hrs: observation x12 hrs, US and repeat CBC if no improvement

Pain ≥24 hrs, ultrasound |
| 26-50% | Moderate      | 14%        | Ultrasound recommended as first line imaging Admit for observation if equivocal                       |
| 51-75% | Moderate      | 14%        | Ultrasound recommended as first line imaging; CT if equivocal                                         |
| 76-90% | Moderate high | 2%         | Consult surgery, consider imaging                                                                     |
| >90%   | High          | 2%         | Consult surgery, imaging not required                                                                 |

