### c) Recommendations by Risk Group

The below table describes recommendations used in the KP RISTRA full CDS by risk threshold.

| MD Gestalt | Risk Stratification | Risk score | Clinical recommendations                                                                                                                |
|------------|---------------------|------------|-----------------------------------------------------------------------------------------------------------------------------------------|
| <=10%      | None                | NA         | Outpatient, no diagnostic imaging                                                                                                       |
| >10%       | Risk Stratification | <5%        | No imaging; outpatient follow-up                                                                                                        |
|            |                     | 6-15%      | Consider Observation; US if pain persists; outpatient follow-up                                                                         |
|            |                     | 16-25%     | Pain +<24 hrs: Observation; US if pain persists

Pain >24 hours: US and/or surgery consult; Admit for observation if US equivocal |
|            |                     | 26-50%     | Ultrasound and/or surgery consults recommended as first line imaging; observation if US equivocal                                       |

|  |  |        |                                                              |
|--|--|--------|--------------------------------------------------------------|
|  |  | 51-75% | US and / or surgery recommended, consider CT if US equivocal |
|  |  | >75%   | Consult surgery, imaging not routinely required              |

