#### Imported Information

Date of Index Emergency Department visit : [index\_er\_date]

Date of Index date + 7 days (pre-populated in Excel) : [index\_7days]

Gender : [gender]

HealthPartner's date of discharge

\_\_\_\_\_  
(MDY)

Which HP hospital was patient at?

- ☐ Regions
- ☐ Lakeview
- ☐ Westfield
- ☐ Hudson
- ☐ Methodist
- ☐ Amery

Was patient transferred to Children's?

- ☐ Yes
- ☐ No  
(Came to Children's from HP facility within 1 day)

Date and time of Children's ED visit

\_\_\_\_\_  
(MDY H:M)

How did the patient arrive at Children's ED?

- ☐ Car
- ☐ EMS
- ☐ Public Transportation
- ☐ Other

If other, how did the patient arrive?

\_\_\_\_\_

Did the patient have surgery during this visit?

- ☐ Yes
- ☐ No

What date and time was the operation?

\_\_\_\_\_  
(MDY H:M)

Did the patient have surgery for appendicitis during this visit?

- ☐ Yes
- ☐ No

What date and time was the surgery for appendicitis performed?

\_\_\_\_\_  
(MDY H:M)

Was this a negative appendectomy?

- ☐ Yes
- ☐ No

(from the pathology report)

(Key Words for Negative Appendectomy: No evidence for neutrophil invasion of tissue, lymphoid hyperplasia present with no evidence for appendicitis, no serosal injection present)

What does pathology report indicate?

\_\_\_\_\_

Final Diagnosis for this visit

- ☐ Appendicitis
  - ☐ Perforated Appendicitis (from operative note)
  - ☐ Medical Diagnosis
  - ☐ Other Surgical
- (Perforation Key Words: Ruptured appendix, abscess noted in the right lower quadrant, purulent material in abdomen, likely perforated appendicitis, or "complex appendicitis")

What did the operative note indicate?

(Perforation Key Words: Ruptured appendix, abscess noted in the right lower quadrant, purulent material in abdomen, likely perforated appendicitis, or "complex appendicitis")

Which medical diagnosis

- ☐ Non-specific abdominal Pain
- ☐ Constipation
- ☐ Gastritis
- ☐ Gastroenteritis
- ☐ Mesenteric Adenitis
- ☐ PID
- ☐ Renal Stone
- ☐ UTI
- ☐ Other Medical Diagnosis

Did the patient have any of the following surgical emergencies during this visit?

- ☐ Ovarian torsion
  - ☐ Testicular torsion
  - ☐ Abdominal tumor
  - ☐ Intussusception
  - ☐ Volvulus
  - ☐ Ectopic pregnancy
  - ☐ N/A
- (Check all that apply)

Did the patient receive imaging at Children's during this visit?

- ☐ Yes
- ☐ No

What imaging studies did the child receive?

- ☐ Xray
- ☐ Ultrasound
- ☐ CT
- ☐ MRI

Did any of the following medical emergencies occur during this visit?

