| CT_order        | num(8) | 1=Yes
0=No                                                                                                                                                                                                                                                                                                                                                                                                                                                                                                                                                                                                                                              | CT of abdomen ordered for this ED visit                |
| US_order        | num(8) | 1=Yes
0=No                                                                                                                                                                                                                                                                                                                                                                                                                                                                                                                                                                                                                                              | Ultrasound of abdomen ordered for this ED visit        |

|                 |        |               |                                                      |
|-----------------|--------|---------------|------------------------------------------------------|
| Appendicitis_Dx | num(8) | 1=Yes
0=No | Appendicitis diagnosis associated with this ED visit |
| Perforation_Dx  | num(8) | 1=Yes
0=No | Perforation diagnosis associated with this ED visit  |

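### The CT and total-imaging outcomes stop at the index ED, so the trial cannot tell an avoided scan from one done later; a 7-day any-setting analysis should be added

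*Combined protocol and SAP*

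**What the plan says.** Hypothesis 2 (section 2a) sets no limit on place: intervention patients "will be less likely to undergo a CT examination". Its measure in section 6b is narrower. Receipt of an abdominal or pelvic CT "during the index ED visit will be determined through completed orders in Epic", and "Only CTs ordered in the ED will be included". Hypothesis 3 adds ultrasound under the same restriction. The Appendix E field, listed with the Hypothesis 1 variables, matches: "CT of abdomen ordered for this ED visit".

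In the same section, the Hypothesis 4 text recognises that "by discouraging CT, the CDS may result in prolonged ED or inpatient observation" and uses this to justify costing all care over the following 7 days. The CT and ultrasound outcomes are not extended in that way, and no episode-level imaging outcome or sensitivity analysis is specified.

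The recommendation tables contain outputs that can move the work-up out of the ED: at HealthPartners (Appendix A, section d), "Admit for observation if equivocal" in the 26-50% risk group; at Kaiser Permanente Northern California (KPNC; Appendix B, section c), "Admit for observation if US equivocal" in the 16-25% group with pain beyond 24 hours.

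**The concern.** The stated benefit is less ionizing radiation for the individual child. A scan that moves from the ED to the ward, to the receiving hospital or to a return visit gives no such benefit, yet the measure records it as a scan not done. The intervention acts on the pathway that determines where a later scan would happen, so displacement could change in intervention EDs after go-live and not in control EDs. The difference-in-differences estimate would then include relocated scans as part of the reduction. At stake is whether a positive result supports a statement about CT exposure or only about CT ordering in the index ED.

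**Working it through.** **Inputs.** Baseline CT rate 30%; planned relative decreases 25% and 20%; 14 EDs; intra-class correlation 0.05; 300 patients per ED per year expected (all from Sample size and power). Pre-period 6 months and post-period 24 months (section 3). Pre/post by arm interaction in a log-linear GEE (section 6, Hypotheses 2 and 3).

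**The plan's own figures.** Planned absolute effects: 0.30 × 0.25 = 7.5 points (30% to 22.5%) and 0.30 × 0.20 = 6 points (30% to 24%). Table 1 does not state its method. It is approximately recovered by a difference-in-differences with 7 EDs per arm, site effects cancelling and residual variance (1 − 0.05) × p(1 − p). At 300 per ED per year (150 pre, 600 post) and a 25% decrease:

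SE² = (0.95/7) × [0.21/150 + 0.21/600 + 0.21/150 + (0.225 × 0.775)/600] = 0.000467, so SE = 0.0216; power = Φ(0.075/0.0216 − 1.96) ≈ 93.5%, against 91% stated.

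Across the three rows this gives 80.9/61.9, 93.5/79.1 and 98.0/89.3, against 80/63, 91/82 and 98/86. The largest gap is 3.3 points. Table 1 is not disputed here; it only supplies a scale.

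**Which scans are counted.**

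| Where the CT is ordered | Counted in H2/H3? | Planned source that could show it |
|---|---|---|
| Index ED, including during ED observation | Yes | Epic orders |
| Inpatient unit after admission | No | Hypothesis 4 encounter table (CPT-4 codes, Clarity and claims) |
| Receiving hospital after transfer | No | Member claims; Children's form ("What imaging studies did the child receive") |
| Return visit within 7 days | No | Hypothesis 4 table; Children's form, up to 7 return visits |

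A repeat ED visit for abdominal pain within 7 days is excluded as a new index visit (section 3a; Appendix E, Prior_ED_Visit), so a CT at that visit enters neither outcome.

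**Effect of displacement.** Let E be the proportion with a CT in the index ED, and L the proportion with none there but one later, through day 7. On the absolute scale the episode rate is E + L, so the episode effect is the difference-in-differences in E plus that in L. Define f as the net rise in L in the intervention arm (beyond any change in control) divided by the apparent fall in E. Then, starting from L = 0:

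true relative reduction = observed reduction × (1 − f)

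| f (assumed) | Episode CT rate when the ED rate falls 30% to 22.5% | Truth behind an observed 25% | Truth behind an observed 20% |
|---|---|---|---|
| 0 | 22.5% | 25% | 20% |
| 0.1 | 23.25% | 22.5% | 18% |
| 0.2 | 24.0% | 20% | 16% |
| 0.5 | 26.25% | 12.5% | 10% |

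At f = 0.2 the plan's larger effect becomes its smaller one, which Table 1 gives 82% power instead of 91% at 300 patients per ED per year.

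**Stable displacement.** If L is the same in both arms and both periods, it cancels exactly on the absolute scale and nearly so on the ratio scale of the log-linear model. With 2 points assumed throughout, the ratio is 24.5/32 = 0.766, a 23.4% reduction instead of 25%.

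**The case against.** The strongest reply is that the measure fits an intervention aimed at ED ordering, and that nothing in the documents shows displacement differing by arm. Several parts of this stand.

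- **Bias in favour of the intervention is not established.** A reader might infer that scan location depends on arm and that the estimate is therefore biased upwards. The protocol says only that more observation may result. Only a differential change after go-live matters, and its sign is open: if advice against imaging in the lowest-risk groups also lowers admissions or transfers, later CTs fall too. Then f is negative and the ED-only result understates the benefit.
- **The routes are narrower than they look.** Some observation takes place in the ED, a surgical consultation does not itself move the order, and a CT ordered in the ED still counts. Explicit admission appears in one HealthPartners row (14% of patients) and one KPNC sub-row.
- **No size can be read from the documents.** One might suppose that 2 to 3 of every 100 intervention patients have their CT moved, so that 2/7.5 = 27% to 3/6 = 50% of the planned effect is artefact. That input has no source and should carry no weight.
- **It cannot be said that the trial already collects most relocated scans.** The HealthPartners chart form has no imaging item, the Children's form records CT without body region, claims cover members only, and the member share is not given.
- **CT use is not formally labelled the primary outcome.** It is the hypothesis that was powered, and section 3a refers to the CT and ultrasound analyses as primary.

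Planned utilization, disposition, length-of-stay and return-visit data would show some displacement, but not as CT counts. None of these points lets the defined outcome separate an avoided scan from a relocated one.

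**Conclusion.** The concern holds as a limit on what the outcome can show, and as a conditional risk of bias. As defined, Hypotheses 2 and 3 score imaging after admission, after transfer or on return within 7 days as no imaging, and no planned analysis corrects for this. If such imaging rises in intervention EDs relative to control EDs after go-live, the reduction in CT exposure is overstated by the factor 1/(1 − f). Displacement that is stable or equal between arms largely cancels. The range of f from 0 to 0.5 is assumed, and the documents support neither a value nor a sign. The point rests on the wording of the outcome definition and does not depend on the power figures.

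**What to change.** - **Keep** the ED-only measure for Hypotheses 2 and 3, and word its conclusion as CT (or imaging) use in the index ED.
- **Add** a pre-specified secondary analysis with the same model: any abdominal or pelvic CT, and CT or ultrasound, from index arrival through day 7 in any captured setting. Apply the existing CPT lists to the Hypothesis 4 encounter table, which is specified to 30 days and would be cut at day 7. Supplement it with the Children's form after checking body region.
- **Order:** first in HealthPartners and KPNC members, for whom the plan expects complete capture, then in all patients.
- **Report** by arm and by route (inpatient, receiving hospital, return visit). Analyse patients by the arm of their index ED; this matters because four pediatric surgical hubs are among the 11 KPNC study sites and a hub may be in the other arm.
- **Interpret** by showing the 7-day estimate and confidence interval beside the ED-only result, without a significance gate.
- **Reconcile** the handling of transferred patients whose outside records are unavailable. Section 3a retains them in the imaging analyses, while sections 6b and 7a exclude them from primary analyses; transfer is one of the displacement routes.

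The cost is mainly programming on planned data, with some linkage and a body-region check. No new patients or visits are needed. The downside is incomplete capture for non-members seen elsewhere, which the members-only analysis makes visible.

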#### a) Exclusion Criteria

Using data from the EHR and gathered from triage-based prompts introduced at all participating EDs, we will identify patients with a current pregnancy, previous abdominal surgery, trauma, cystic fibrosis, sickle cell anemia, inflammatory bowel disease, or other selected comorbidities at the prime site, or with an ED visit for abdominal pain in the prior 7 days. These patients will be excluded from the study cohort. As described below, based on responses to the initial screening questions, patients with >120 hours of abdominal pain or patients with no right sided or generalized abdominal pain will also be excluded from the risk score calculation and further analyses.

If patients are transferred to an outside facility (outside of KPNC or HealthPartners networks) for surgery *and* we are unable to review their operative and pathology notes, they will be excluded from the safety analyses. These patients will be retained in the primary analyses, evaluating the use of CT or US, with the diagnosis of appendicitis or not appendicitis assigned based on provider impression and imaging available at the time of ED discharge / transfer.

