We anticipate some variation in billing practices across study sites and variation in patterns of care. Thus, we will examine health care utilization from two perspectives, distinguished by the dataset. The first analytic dataset will include the entire sample and will focus on ED and other hospital costs incurred at study sites. This analysis will focus upon the impact of the Appy-CDS from a single hospital perspective. The second analytic dataset will be limited to those insured by HealthPartners and KPNC. This tightened sample will provide complete capture of all billed and reimbursed medical care and accurately estimate the risks of ED re-visit and total episode costs and examine the Appy-CDS' impact across the broader health care system.

Similarly, two utilization measures will be employed. The first will be Total Cost Relative Resource Value units (TCRRVs), which are endorsed by the National Quality Form (NQF) to measure costs for the full study cohort. TCRRVs are based on Centers for Medicare and Medicaid Services (CMS) relative value units (RVUs) but extend RVU measures to include inpatient, outpatient surgery, ED services, and scheduled outpatient, professional, and pharmacy services that do not have CMS RVU weights. Because TCRRVs value services similarly to RVUs, TCRRVs are convertible to dollars using the Medicare cost factor and have been used by our team in several recent econometric studies. The second measure will be billed amounts, or the total dollars billed, including patient co-pays and deductibles. The use of billed amounts allows comparison between hospitals in HPMG (open access) and KPNC (total cost per member) systems. Although we do not anticipate significant differences in adverse event rates post Appy-CDS implementation if these do occur, we will determine the long term health care cost and quality of life impact by developing a simulation model of the Appy-CDS implementation using established techniques.

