**Appendiceal perforation, negative appendectomies, and missed appendicitis** (safety outcomes): Although it is unlikely that the Appy-CDS will significantly increase rates of adverse events, the following clinical or safety outcomes will be monitored both before and during the full Appy-CDS intervention. *Appendiceal perforation* will be evaluated in patients who undergo appendectomy based on chart review of the surgeon's intra-operative note. As in our previous work, perforation will be defined by keywords in the operative report (presence of abscess, peritonitis, complex appendicitis, or purulent material). In addition, we will review all charts for patients with a discharge diagnosis of perforated appendicitis (ICD-9 540.1) who do not undergo an appendectomy during their index hospitalization, because a subset of patients with appendiceal perforation (4% in our previous multicenter cohort, unpublished data) will be admitted for intravenous antibiotics and undergo an interval appendectomy 6-12 months later. *Negative appendectomies* are appendectomies in which the pathology report reveals no evidence of appendiceal inflammation. This will be determined via review of pathology reports. *Missed appendicitis* is when a patient presents for the evaluation of abdominal pain, is discharged home, and returns within 1 week with appendicitis. Missed appendicitis will be identified through review of automated EHR data for all patients with appendicitis. As described above, under exclusion criteria, patients who are transferred for definitive care and whose final pathology and surgical reports are not available will not be included in the assessment of safety outcomes.

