## 7) Reporting and Data Storage

### a) Capturing Transfer Patients

One of the unique challenges of this project at the prime site is that many children in this age group are transferred to another hospital for additional follow up or surgery. A subset of patients presenting to a HealthPartners or HealthPartners affiliated ED who are eligible for Appy CDS will most likely be transferred to Children's Hospitals of Minnesota for definitive surgical care. In order to evaluate final diagnoses for these patients, a process for identifying and linking patients has been developed and is outlined in Figure 3.

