| Negative appendectomy   | An appendectomy occurring in the setting of acute abdominal pain with normal pathology, no evidence of inflammation, where an appendectomy is the only surgical procedure performed. | 
 
1. Chart review of appendix pathology reports
 
2. Does not include incidental appendectomies, if appendectomy is part of more extensive abdominal procedure
 
                                                                                                                                                                                                                                                                                                                     |
| Missed appendicitis     | A patient who is evaluated in a study ED for acute abdominal pain is discharged home and then returns, within 7 days, with appendicitis                                              | 
 
1. Review of EHR and claims data for ICD-10 codes: K35, K35.2, K35.3, K35.8, K35.89, K36, K37 within 12 days of index ED visit, to account for diagnosis date to be hospital discharge date. Followed by manual review to confirm whether appendicitis was within 7 days of index ED visit.
 
                                                                                                                                                                                                    |

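### The exclusion of out-of-network transfers without operative and pathology notes should apply outcome by outcome; as worded it also covers missed appendicitis and other outcomes that are not found from those notes

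*Combined protocol and SAP*

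**What the plan says.** Section 3a (Exclusion Criteria) deals with patients sent for surgery outside both health systems. Where "we are unable to review their operative and pathology notes, they will be excluded from the safety analyses". The same paragraph keeps them in the CT and ultrasound analyses, using the diagnosis at ED discharge or transfer.

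Section 6b (Measurement of Outcomes, safety paragraph) defines perforation, negative appendectomy and missed appendicitis, then refers back to that rule: transferred patients "whose final pathology and surgical reports are not available will not be included in the assessment of safety outcomes". No outcome is exempted.

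Missed appendicitis in section 6b is a child who presents with abdominal pain, "is discharged home, and returns within 1 week with appendicitis". On the source, section 6b says "Missed appendicitis will be identified through review of automated EHR data for all patients with appendicitis". Table 4 gives the source as "Review of EHR and claims data for ICD-10 codes", followed by manual review of whether the 7-day window was met.

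On transfers at the prime site, section 7a says that "many children in this age group are transferred to another hospital for additional follow up or surgery".

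**The concern.** The rule works by patient, while the reason for it works by outcome. Missing operative and pathology notes prevent classification of a negative appendectomy, and of perforation in an operated child. They do not prevent detection of a return visit, an ICU stay, a delayed diagnosis from Table 6, or a coded appendicitis diagnosis within 7 days of discharge home.

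Two things are at stake. First, missed appendicitis is the harm most directly linked to a tool that discourages imaging, and the human-subjects section supports the consent waiver partly by undertaking to monitor missed cases and report them to the IDMC. Second, exclusion depends on an event after randomisation, among children sent for surgery. The recommendation tables in Appendices A and B steer observation and surgical consultation by risk band, so transfer could differ between arms. The documents do not show that it does.

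**Working it through.** **Step 1. Which safety outcomes need the notes?**

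| Outcome | Stated source | Operative or pathology note named? |
|---|---|---|
| Perforation, operated (Table 4) | Surgeon's operative note | Yes |
| Perforation, not operated at first admission (Table 4) | Codes K35.2, K35.3 with admission for intravenous antibiotics | No |
| Negative appendectomy (Table 4) | Pathology report | Yes |
| Missed appendicitis (Table 4) | ICD-10 codes in EHR and claims, manual review of timing | No |
| ED returns, ICU admission (Table 5) | Billing, EHR, CPT codes, chart review | No |
| Other missed emergencies (Table 6) | ICD-10 codes, manual review for delay | No |

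Section 9 lists the proposed safety outcomes in Tables 4 to 7, so the reference in section 3a to the safety analyses naturally reaches Tables 5 and 6 as well as Table 4.

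**Step 2. Which child is affected?**
- Transferred at the index visit: never discharged home, so not a missed-appendicitis event under section 6b or Table 4.
- Discharged home, returns within 7 days with appendicitis, then transferred out of network with notes unobtained: meets the definition, and is removed by the wording of sections 3a and 6b.

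**Step 3. Does another passage put that child back?** The diagnosis-at-transfer fallback serves the imaging analyses (3a) or sensitivity analyses for patients dropped from the primary analyses (6b Hypothesis 1 paragraph, 7a). The quarterly review of missed eligibles in section 9 looks for appendicitis but is not said to feed the between-arm safety rates. So no passage restores the child to the comparison.

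**Step 4. Scale for missed appendicitis.** The plan states no figure to reproduce: it gives neither a missed-appendicitis rate nor a count of unobtainable notes. Both are assumed here. If the true rate is p and a share L of missed cases is removed from numerator and denominator, the observed rate is p(1 − L)/(1 − pL). Take 0.5% in control and 1.0% in intervention, a true excess of 0.50 points:

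| L | Lost in both arms | Lost in intervention only |
|---|---|---|
| 10% | 0.45 | 0.40 |
| 20% | 0.40 | 0.30 |
| 30% | 0.35 | 0.20 |

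For L = 20%: intervention 0.01 × 0.8/(1 − 0.002) = 0.802%; control 0.005 × 0.8/(1 − 0.001) = 0.400%; difference 0.40. With loss in intervention only, 0.802 − 0.500 = 0.30. With loss in control only, 1.000 − 0.400 = 0.60, so a one-sided loss can also exaggerate harm. At assumed rates of 0.3% against 0.6%, or 1.0% against 1.5%, equal loss of 10–30% again shrinks the excess by about 10–30%.

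At HealthPartners, Table 7 (an example table) projects 684 + 528 = 1,212 children over two years. At an assumed 0.5–1% that is about 6 to 12 missed cases, so one lost case is 1/12 = 8% to 1/6 = 17% of them.

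**Step 5. What all/none bounds for perforation would look like.**
- Appendicitis share among flagged children: 2,634/(0.5 × 24,603) = 21.4%, from the sample size section, assuming every case falls in the flagged half.
- HealthPartners cases: 1,212 × 0.214 ≈ 260.
- Perforation rate: 178/778 = 22.9%, from the pilot.
- With e cases lacking notes, the bounds are 0.229(260 − e)/260 and [0.229(260 − e) + e]/260.
- Assumed e = 26 (10%): 20.6% to 30.6%. Assumed e = 78 (30%): 16.0% to 46.0%.

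**The case against.** Four arguments on the other side have weight.

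*A reader might infer that every transferred child is a harm that disappears.* The documents do not support that. They mostly describe transfer from the ED of first presentation, and those children cannot be missed cases. The Children's chart form separates transfers from returns and records a final diagnosis for each return. However, section 3a does not limit the rule to index-visit transfers, so the child in Step 2 remains covered by its wording.

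*A reader might infer that missed appendicitis plainly needs no pathology.* That is too strong. The Hypothesis 1 paragraph in section 6b defines appendicitis in operated patients by pathology terms, and section 7a excludes unverified transfers from the primary analyses because appendicitis cannot then be confirmed. On that definition such a child is an unconfirmed case. Table 4, the outcome-specific definition, sets no such condition. The two passages conflict and need reconciling.

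*The numbers may be small.* The rule covers only transfers outside both systems. Children's, the main outside recipient, is linked monthly; final diagnoses and pathology are sought from receiving institutions generally; KPNC has four surgical hubs among its sites. This stands. The statement that many children are transferred concerns all transfers, not those without notes.

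*Oversight already exists.* Missed eligibles, which include patients whose final diagnosis is unavailable after transfer, are reviewed quarterly and reported to the IDMC, and potential adverse events are reviewed at site. So these cases are not necessarily hidden from the IDMC. They are still absent from the between-arm rates.

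*A reader might also infer a bias in favour of the intervention.* Nothing in the documents shows that loss differs by arm, and Step 4 shows that it could act in either direction.

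**Conclusion.** The exclusion is wider than its reason. It is defensible for negative appendectomy and for perforation in operated patients. For missed appendicitis, returns, ICU admission and the Table 6 outcomes it discards children whose status the plan's own listed sources could often establish, and it can remove a child from the missed-appendicitis rate that he or she meets.

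The size cannot be determined from the documents. The loss shares and missed-appendicitis rates above are assumptions, the HealthPartners counts come from an example table, and the perforation rate comes from a pilot in children's hospital EDs. The effect may be slight. Because missed cases are expected to be few, even one or two lost cases would matter within HealthPartners. This is a correction to a stated rule, not evidence that the safety comparison is biased.

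**What to change.** 1. In sections 3a and 6b, limit the exclusion to negative appendectomy and perforation in operated patients.
2. Keep these children in missed appendicitis, ED returns, ICU admission and the Table 6 outcomes, using the sources already listed.
3. Reconcile the pathology definition in section 6b with Table 4: count cases supported only by codes or by the diagnosis at transfer as *probable* missed appendicitis, and add a sensitivity analysis restricted to confirmed cases.
4. Where a nonmember's outside care cannot be observed, record the outcome as unknown, not as a non-event. The plan's Hypothesis 4 text claims full capture only for the insured subset: "This tightened sample will provide complete capture of all billed and reimbursed medical care".
5. For perforation, add a sensitivity analysis using the diagnosis at transfer or codes K35.2 and K35.3, with all/none bounds.
6. Report the number excluded, by arm and period, to the IDMC.

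The cost is a wording change in two sections, a rule for probable and unknown outcomes, and sensitivity tables built mostly from data already being extracted. The downside is that code-based cases are less certain than note-confirmed ones, and capture remains incomplete for nonmembers; items 3 and 4 make both visible.
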